### Histological analyses

Sections will be stained with hematoxylin and eosin (H&E) in order to quantify damaged myofibers [48]. Myofibers indicating loss of the physiological outline, sarcolemmal damage, mononuclear cell infiltration and centrally located nuclei will be expressed as a percentage of the total number of myofibers.

### Immunofluorescence

Muscle cross-sections (7 μm) will be allowed to air dry at room temperature for 30 min. For fiber-type-specific SCs analyses, samples will be stained with appropriate primary and secondary antibodies against specific antigens such as, Pax7, MyoD, myosin heavy chain type II, and laminin as described previously [49–51]. For fiber-type-specific M1 (pro-inflammatory) and M2 (anti-inflammatory) macrophage quantification, muscle cross-sections will be stained with appropriate primary and secondary antibodies against CD11b^+^, CD206^+^ and laminin as described previously [52]. Nuclei will be visualized with 4′,6-diamidino-2-phenylindole (DAPI) contained in the mounting media prior to coverslipping. The specificity of staining will be verified using negative controls. Slides will be viewed using an Olympus BX41 microscope equipped with appropriate filters and a high-resolution fluorescent camera. Images will be captured and analyzed using the Image-Pro Plus v6.0 software. All images will be obtained with the 20X objective. Myofiber cross-sectional area (CSA), fiber type distribution (% type I and II fibers), myonuclei content (DAPI^+^ cells), fiber-type-specific SCs content and activation status (Pax7^+^ and MyoD^+^ cells per myofiber) and M1 (CD11b^+^/CD206^–^cells) and M2 (CD11b^+^/CD206^+^ cells) macrophage content will be determined. The SCs content and activation will be determined via the colocalization of Pax7 and DAPI and/or the colocalization of Pax7, MyoD and DAPI within the laminin border. M1 and M2 macrophage content will be determined via the colocalization of CD11b, CD206 and DAPI.

### Quantitative RT-PCR

Total RNA will be isolated from 10–20 mg of frozen muscle tissue using the NucleoSpin RNA Plus kit (Machery-Nagel, Bethlehem, PA, USA), according to the manufacturer’s instructions, at a final volume of 80–120 μL. RNA concentration (ng/ml) and purity (260/280) will be measured spectophotometrically (Hitachi UV/VIS; Hitachi Instruments Inc., Tokyo, Japan). Then samples will be reverse transcribed using a PrimeScript 1st strand cDNA synthesis kit (Takara Mountain View, CA, USA) in 20-μl reaction volumes, according to the manufacturer’s protocol. Quantitative RT-PCR reactions will run in triplicates containing RT Sybr Green qPCR Master Mix. Primers for Myf5, MyoD, myogenin, MRF4, myostatin and gyceraldehyde 3-phosphate dehydrogenase (GAPDH) will be purchased and mRNA expression levels will be calculated using the 2^−ΔΔCt^ method. Fold changes from baseline will be calculated using the ΔΔC_t_ method and normalization will be performed using the housekeeping gene GAPDH [53].

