**Methods/design:**

Based on the SCs content in their vastus lateralis skeletal muscle, participants will be classified as either high or low respondents. In a randomized, double-blind, crossover, repeated-measures design, participants will then receive either placebo or *N*-acetylcysteine (alters redox potential in muscle) during a preliminary 7-day loading phase, and for eight consecutive days following a single bout of intense muscle-damaging exercise. In both trials, blood samples and muscle biopsies will be collected, and muscle performance and soreness will be measured at baseline, pre-exercise, 2 and 8 days post exercise. Biological samples will be analyzed for redox status and SCs activity. Between trials, a 4-week washout period will be implemented.

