## Methods/design

### Study overview and design

The methods and ethics of the present study have been approved by the Institutional Review Board of the University of Thessaly (ref. number 1387) and procedures are in accordance with the Declaration of Helsinki, as revised in 2013. The SpEED study incorporates a randomized, two-trial (NAC vs placebo), cross-over, double-blind, repeated-measures design. Participants who will fulfill the inclusion criteria will have their body mass, height, resting metabolic rate (RMR), body composition, muscle strength, soreness and maximal oxygen consumption (VO_2max_) measured. Since protein and antioxidant consumption as well as systematic physical activity (PA) and/or exercise may affect SCs responses and/or redox status, participants’ daily nutrient intake (via a 7-day diet recall with emphasis on protein and antioxidant intake) and PA levels (via accelerometry instrumentation) will be monitored for a week before the inception of the study [24–26]. Then, a 2-week adaptation period (only before the first trial) will be applied to adjust (through a balanced diet, using RMR values and daily energy expenditure measurements) protein and antioxidant intake at the levels required by current Recommended Dietary Allowances (RDAs) (0.8–1 g of protein/kg/day; 900 mg/day of vitamin A; 90 mg/day of vitamin C; 600 IU/day of vitamin D; 15 mg/day of vitamin E; 11 mg/day of zinc; 400 mg/day of magnesium and 55 mg/day of selenium) [27, 28]. This dietary protocol will be designed and implemented by a registered dietician. During the same time-frame, familiarization with experimental procedures will be provided.

Evidence exists that skeletal muscle growth and myogenic potential is directly related to its basal SCs content [24, 29]. As such, volunteers will provide a resting (they will abstain from any exercise or intense PA for at least 5 days prior to sampling) muscle biopsy sample (baseline sampling) from their vastus lateralis muscle (of their dominant limb) and based on its SCs content will be stratified to either high (HR) or low (LR) respondents. Participants will be stratified as HR or LR using a K-means cluster analysis. Blood sampling and performance measurements will also be performed at baseline.

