Following stratification to the HR and LR groups, volunteers of each group will then perform two trials in a randomized order: (1) NAC ingestion and (2) placebo ingestion. NAC or placebo will be consumed before (a 7-day loading phase) and after (immediately post exercise and for eight consecutive days thereafter) an intense eccentric exercise protocol. During both trials, participants will follow the balanced daily dietary protocol of the adaptation period. However, daily dietary intake will be recorded and analyzed during each trial in an attempt to minimize deviations from the prescribed diet. A 4-week washout period will be implemented between trials (dietary intake during this period will also be adjusted according to that applied during the adaptive period). During the entire experimental period, participants will be asked to abstain from any strenuous PA or exercise. Muscle biopsies and blood samples will be collected after overnight fasting before the exercise protocol (pre-exercise sampling) as well as at 2 and 8 days post exercise. Muscle strength and delayed onset of muscle soreness (DOMS) will be evaluated at the same time points. All measurements and collection of biological samples will be performed at the same time of day, in both trials, to prevent circadian rhythm variations. Figure 1 shows the Consolidated Standards of Reporting Trials (CONSORT) diagram of the study and Fig. 2 illustrates the experimental flowchart for the clinical trials.

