**Fig. 2 Fig2:**
[figure not shown]
The experimental flowchart for the clinical trials

The primary outcomes of the study are the SCs-specific markers measured in muscle (Pax7^+^, MyoD^+^ cells per type I/II myofibers), the macrophages’ markers measured in muscle (cluster of differentiation 11b marker (CD11b^+^), cluster of differentiation 206 marker (CD206^+^) cells per myofiber), the myogenesis-related markers measured in muscle (Myf5, MyoD, myogenin, MRF4 and myostatin mRNA expression levels), the cell signaling markers measured in muscle (GPX-3, SOD-2, Trx-1, insulin-like growth factor 1 (IGF-1), Notch1, Wnt3 protein expression levels), and the oxidative stress markers measured in muscle (GSH, oxidized glutathione (GSSG), protein carbonyls (PC) and malondialdehyde (MDA)). The secondary outcomes are the oxidative stress markers measured in blood (total antioxidant capacity (TAC) in serum, GSH, GSSG, catalase (CAT) and hemoglobin (Hb) in red blood cell lysates), and the inflammatory markers measured in blood (C-reactive protein (CRP), tumor necrosis factor alpha (TNF-α), interleukin (IL)-6, IL-8, IL-10), blood creatine kinase activity (CK) as a marker of muscle damage and serum cortisol). Other outcomes include body mass, height, body mass index (BMI), total and regional fat mass, lean mass and body fat, RMR, number of steps/day and time spent at sedentary, light, moderate, vigorous and moderate-to-vigorous PA, total daily energy intake and expenditure, daily intake of carbohydrate, fat, protein, vitamin A, vitamin C, vitamin D, vitamin E, selenium, zinc and magnesium, VO_2max_, knee extensors’ (KE) maximal eccentric and concentric peak torque and DOMS.

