All analyses and reporting of the results will comply with the Standard Protocol Items: Recommendations for Interventional Trials (SPIRIT) Statement for reporting randomized clinical trials (RCTs) [57]. Results of participant’s baseline characteristics and outcome variables (primary, secondary and other) will be summarized using descriptive statistics and will be expressed as mean (standard deviation) or median (range) for continuous variables. Data normality will be examined using the Kolmogorov-Smirnov and the Shapiro-Wilk tests. If our data sets follow normal distribution, parametric tests will be applied. Baseline comparisons on the LR and HR groups (anthropometrics, body composition, strength, VO_2max_, dietary profile, PA) will be performed using a one-way ANOVA test. Time- and trial-effect comparisons within and between trial (NAC or placebo) in the LR and HR groups will be analyzed using a two-way repeated-measures ANOVA test with a Bonferroni correction for pairwise comparisons. If the data normality is violated, non-parametric tests will be applied. Baseline comparisons on the LR and HR groups will be performed using a Kruskal-Wallis test. Time-effect comparisons within trial (NAC or placebo) in the LR and HR groups will be analyzed using a Friedman test accompanied by Wilcoxon signed-rank test for pairwise comparisons. Trial-effect comparisons between trials (NAC vs placebo) in the LR and HR groups will be analyzed using a Kruskal-Wallis test accompanied by a Mann-Whitney *U* test for pairwise comparisons. Pearson’s correlation analysis will also be used to examine possible relations among variables. Correlation coefficients of r < 0.2, 0.2 < r < 0.7 and r > 0.7 will be defined as small, moderate and high, respectively. The level of statistical significance will be set at *p* < 0.05. Effect sizes (ES) and confidence intervals (95% CI) will be calculated on results of all dependent variables using the Hedge’s *g* method, corrected for bias. ES will be interpreted as none, small, medium-sized and large for values 0.00–0.19, 0.20–0.49, 0.50–0.79 and ≥ 0.8, respectively. Multiple-imputation analysis will also be utilized to handle missing data during data collection and sensitivity analyses will be executed to evaluate the robustness of the results [58]. Statistical analyses will be performed using the SPSS 20.0 software (IBM Corp., Armonk, NY, USA).

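### The five primary mRNA outcomes are given only a linear fold-change scale, which is skewed and costs power in the NAC-placebo comparison when biopsies are noisy; ΔCt should be analysed instead

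*Protocol article*

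**What the plan says.** The Study overview and design section lists among the primary outcomes "the myogenesis-related markers measured in muscle (Myf5, MyoD, myogenin, MRF4 and myostatin mRNA expression levels". That is five genes.

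The Quantitative RT-PCR section fixes their scale: "and mRNA expression levels will be calculated using the" 2^-ΔΔCt method, and then "Fold changes from baseline will be calculated using the" ΔΔCt method, normalised to GAPDH. It does not say whether the calibrator is each man's own baseline or a group mean.

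The Statistical analyses and Power calculation section says: "If our data sets follow normal distribution, parametric tests will be applied". The parametric test is a two-way repeated-measures ANOVA with Bonferroni-corrected pairwise comparisons. If normality is violated, NAC and placebo are compared by Kruskal-Wallis and Mann-Whitney tests. The time levels of the ANOVA are not listed.

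On sampling, the Study overview and design section describes a "muscle biopsy sample (baseline sampling) from their vastus lateralis muscle (of their dominant limb"), taken before stratification. Biopsies within each trial come "before the exercise protocol (pre-exercise sampling) as well as at 2 and 8 days post exercise". The Abstract can be read differently: "In both trials, blood samples and muscle biopsies will be collected", with baseline listed among the time points. The Exercise protocol section uses a different limb in each trial.

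**The concern.** ΔCt is a log2 quantity on which biological and technical variation is roughly additive. Raising 2 to that power gives a right-skewed variable and turns additive error into multiplicative error. The calibrator matters most: if it is a man's own single baseline biopsy, a low reading there inflates all his fold values in both trials and a high reading shrinks them. He then gets more or less weight in the NAC-placebo contrast for a reason unrelated to treatment. If one dominant-limb biopsy serves both trials, it is also the reference for the other limb in one of them.

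At stake are the power and interpretability of the treatment contrast for five primary outcomes in groups of about 12 men. Effect sizes computed on the fold scale would also lean on the men whose baseline happened to read low.

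**Working it through.** **Inputs from the protocol.** Group size: 10/(1 − 0.15) = 11.76, which reproduces the protocol's 11.8 and gives 12 per LR or HR group. Significance level: 0.05. The protocol gives no SD or effect for any mRNA marker, so there is no mRNA figure to reproduce.

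**Assumptions.** Within-man (biopsy) SD σ of 0.4, 0.6 or 0.8 Ct; NAC effect δ of 0.6 or 0.8 Ct; normal errors on the log2 scale; own baseline as calibrator, shared by both trials.

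**Why the baseline error stays in.** Write log2 expression (−ΔCt) at baseline as μ + e_B, and at a later time as μ + τ + δ + e_N under NAC and μ + τ + e_P under placebo.
- Log2 difference: δ + e_N − e_P. The person level μ and the baseline error e_B both cancel.
- Fold difference: 2^(τ − e_B) × (2^(δ + e_N) − 2^(e_P)). The common factor 2^τ drops out of a t ratio and μ is gone, but 2^(−e_B) remains as a separate multiplier for each man.

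At σ = 0.6, two men whose baseline readings are one SD below and one SD above their true level differ by a factor of 2^1.2 = 2.3 in that multiplier. At σ = 0.8 the factor is 2^1.6 = 3.0.

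**Skew.** The fold value is lognormal with log variance s² = 2σ²(ln 2)², and its skewness is (exp(s²) + 2)·√(exp(s²) − 1). At σ = 0.4, 0.6 and 0.8, s² = 0.154, 0.346 and 0.615, giving skewness of 1.3, 2.2 and 3.5.

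**Pairwise power, paired t-test, n = 12.** On ΔCt the noncentrality is δ√12/(σ√2). For δ = 0.8 this is 2.771/0.849 = 3.27 at σ = 0.6 (power 84%) and 2.771/1.131 = 2.45 at σ = 0.8 (61%). Simulation gives:

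| δ (Ct) | σ (Ct) | Fold change | ΔCt |
|---|---|---|---|
| 0.8 | 0.6 | about 75% | about 85% |
| 0.8 | 0.8 | 43% | 60% |
| 0.6 | 0.4 | 88% | 92% |
| 0.6 | 0.6 | 51% | 61% |
| 0.6 | 0.8 | 27% | 39% |

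Rejection under no effect is 3.5 to 4.7% on fold change and about 5% on ΔCt.

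**Trial-by-time ANOVA, n = 12, uncorrected.** Assumed placebo rise of 1 log2 unit at day 2 and 0.5 at day 8, with NAC raising expression at both.

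| Time levels | δ | σ | Fold | Log2 scale |
|---|---|---|---|---|
| Pre, day 2, day 8 | 0.6 | 0.4 | 84% | 71% |
| Pre, day 2, day 8 | 0.6 | 0.6 | 39% | 36% |
| Pre, day 2, day 8 | 0.6 | 0.8 | 19% | 23% |
| Pre, day 2, day 8 | 0.8 | 0.6 | 66% | 60% |
| Pre, day 2, day 8 | 0.8 | 0.8 | 33% | 37% |
| Baseline added | 0.75 | 0.5 | 94% | 94% |
| Baseline added | 0.75 | 0.8 | 47% | 53% |
| Baseline added | 0.75 | 1.1 | 21% | 30% |

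At smaller SDs the fold scale can win here because the assumed rise enlarges the day-2 contrast on the linear scale. With a flat or falling placebo course, or with NAC lowering expression, the ordering at 0.4 to 0.6 can reverse. With baseline included, type I error is 4.5 to 7.3% on folds and 6.1 to 6.4% on log2.

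**Normality test.** At n = 12 Shapiro-Wilk rejects the folds in about 20%, 38% and 55% of samples at σ = 0.4, 0.6 and 0.8, against about 5% on the log2 scale. After rejection the planned comparison is Mann-Whitney. For δ = 0.6 its power is 69%, 31% and 15%, against 89%, 56% and 36% for a paired Wilcoxon test on ΔCt.

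**The case against.** Three stronger readings are tempting, and the protocol does not support them.

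- **Zero baseline variance breaks the ANOVA by construction.** This needs an own-baseline calibrator and baseline kept as a time level; neither is stated. The within-trial biopsies are pre-exercise, day 2 and day 8, and these may well be the ANOVA levels. Nor is the fold scale the cause: own-baseline ΔΔCt is a constant 0 at baseline, just as the fold is a constant 1.
- **The analysis is invalid.** Parametric tests are conditional on normality, and type I error is close to nominal or similar on the two scales.
- **The main test always loses power.** The ANOVA results above show otherwise at SDs of 0.4 to 0.6.

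Two further objections carry some weight. The unpaired fallback is a separate defect affecting every non-normal marker, and within it taking logs of the same ΔΔCt values changes nothing, because ranks are unaffected. The skew only makes that branch more likely. Also, transformations are often left to the analysis plan, and the fold-change sentence sits in a laboratory section. But the article does not leave the scale open: it names one, for primary outcomes, and its statistical section does not replace it.

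**Conclusion.** The point holds as one of efficiency and interpretability, not validity. The only scale named for five primary outcomes is right-skewed and, with an own-baseline calibrator, carries the error of the baseline biopsy into the treatment contrast. For the pairwise NAC-placebo comparison the cost is about 10 percentage points of power at an SD of 0.6 Ct and about 17 at 0.8 Ct (0.8-Ct effect, n = 12), and almost nothing at 0.4. For the trial-by-time interaction the loss is consistent only from about 0.8 Ct upward; below that it depends on the time course and on the direction of the effect. The normality test is a weak safeguard: at these sample sizes it often misses the skew, and when it detects it, the paired structure is lost. All these sizes rest on assumed SDs and effects, because the protocol gives none for mRNA. The number of baseline biopsies is also not settled, since the Abstract and the Methods can be read differently.

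**What to change.** State in the statistical section that mRNA is analysed as ΔCt (target minus GAPDH, log2 scale, not calibrated to baseline) at pre-exercise, day 2 and day 8, in the repeated-measures model already planned. Back-transform the model differences to fold changes with 95% CI for presentation only. Leaving baseline out as a time level removes any constant level, which taking logs of ΔΔCt alone would not do.

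Reconcile the Abstract with the Study overview and design section on whether there is one baseline biopsy or one per trial. The unpaired non-parametric comparison of NAC and placebo deserves its own correction to a paired test; it should not be left as the fallback for ΔCt, where between-man differences are not subtracted out.

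The cost is one sentence in the analysis plan and one clarification of the sampling scheme, with no new laboratory work. The article says the trial has not yet commenced, so the change can be made before any data are seen.

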### Western blotting

Changes in protein expression levels of GPX-3, SOD-2 and thioredoxin Trx-1 (related to SCs homeostasis), IGF-1, Notch1 and Wnt3 (related to SC mobilization) will be analyzed by immunoblotting. Muscle samples will be homogenized in lysis buffer and then centrifuged (13,000 rpm, 4 °C, 10 min) and the supernatant will be collected. Total protein concentration will be determined using the Bradford method (Bradford Protein Assay; Bio-Rad). Twenty milligrams of protein will be loaded in gradient precast gels (Mini-PROTEAN TGX Gels; Bio-Rad, Hercules, CA, USA) and will be subjected to SDS-PAGE electrophoresis at room temperature. Afterwards, proteins will be transferred to trans-blot stacks using the Trans-blot Turbo transfer system (Bio-Rad, Hercules, CA, USA), blocked for 1 h and incubated with primary antibodies overnight at 4 °C. Membranes will be washed in tris-buffer saline (TBS-T) solution and will be incubated with appropriate secondary antibodies for 1 h at room temperature. Following another washing step (in TBS-T), membranes will be visualized by chemiluminescence and quantified using densitometry. Normalization will be performed with the housekeeping protein GAPDH.

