## Discussion

The present study is designed to assess the impact of redox status on SCs responses and the mechanisms (hormonal regulation, M1 and M2 macrophages, intracellular signaling) associated with their mobilization and function following aseptic skeletal muscle trauma induced by exercise. Nutritional supplementation or medications have been shown to affect SCs biology under traumatic conditions. Hydrolyzed whey protein supplementation and anti-inflammatory medication (ibuprofen) results in increased SCs response and expedites skeletal muscle recovery [25, 48]. Antioxidant supplementation (vitamin C, vitamin E, NAC or combined antioxidants) may attenuate loss of muscle force production and reduce muscle soreness and lipid peroxidation levels but it may also delay recovery suggesting a potential redox-associated mechanism involved in muscle healing [54, 59]. However, this possibility has not been explored in the human skeletal muscle. More specifically, there is no information regarding the redox-dependent mechanism of SCs mobilization and action in human skeletal muscle. It is well established in the literature that thiol oxidation is a major post-translational oxidative modification affecting the cysteine residues in multiple proteins [60]. On the other hand, increased ROS can oxidize GSH leading to irreversible modification [61]. In this sense, low levels of GSH may not only attenuate the antioxidant defense leading to SCs damage but it may also alter cellular redox status drastically. Furthermore, SCs activity is also determined by redox-sensitive cues (cytokines, immune cells, signaling molecules) emerging from the surrounding microenvironment [62]. Supplementation with a powerful GSH precursor, such as NAC, could not only foster GSH levels and thus muscle’s antioxidant potential but also will change myofiber redox balance which is crucial for the redox-dependent regulation of intracellular signaling pathways mediating pro- and anti-inflammatory response to muscle trauma [30]. Our research hypothesis states that NAC-induced change of muscle’s redox status will upregulate SCs availability and mobility under conditions of increased oxidative stress and inflammation in human skeletal muscle. This is of great importance as muscle injury is present in several clinical conditions characterized by increased muscle wasting, atrophy and sepsis that result in physical deterioration and poor quality of life such as in many types of cancer, cachexia, muscular dystrophies, etc. [11, 12]. Consumption of NAC, a potent thiol-based antioxidant, upregulates GSH/GSSG and reduces the respiratory burst and MAPK- and NF-kB-mediated pro-inflammatory cytokine release during inflammation produced by muscle injury [30, 63]. Information derived from this study will elucidate the redox-dependent regulation of intracellular signaling pathways involved in SCs regulation and muscle healing in human skeletal muscle. Therefore, the results of the proposed study should provide information about possible nutritional and/or pharmaceutical interventions to promote SCs function and increase skeletal muscle’s healing potential.

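### Five mRNA and six protein primary outcomes each rest on a single GAPDH reference whose stability over time and between NAC and placebo is assumed

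*Protocol article*

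**What the plan says.** The primary outcomes, listed in the protocol article under Study overview and design, include "Myf5, MyoD, myogenin, MRF4 and myostatin mRNA expression levels" and "GPX-3, SOD-2, Trx-1, insulin-like growth factor 1 (IGF-1), Notch1, Wnt3 protein expression levels", which is five transcripts and six proteins.

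- **mRNA (Quantitative RT-PCR):** "Fold changes from baseline will be calculated" by the ΔΔCt method, and "normalization will be performed using the housekeeping gene GAPDH".
- **Protein (Western blotting):** "Total protein concentration will be determined using the Bradford method", a fixed amount is loaded per lane, and "Normalization will be performed with the housekeeping protein GAPDH".

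No second reference is named for either assay. Total protein is measured to set the load, but it is not named as the normalizer.

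**The concern.** Dividing by a reference is valid only if the reference is constant across the conditions being compared. Here those conditions are time (before and after 300 maximal eccentric contractions) and treatment (NAC or placebo). The trial is designed to disturb the tissue along both.

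- **Time.** The Background describes macrophage infiltration and inflammation after damaging exercise. The Histological analyses section counts fibers with membrane damage and mononuclear infiltration. The mix of cells in the biopsy is thus expected to change.
- **Treatment.** NAC is given to alter redox state, and the Discussion says that it reduces pro-inflammatory cytokine release after muscle injury. Macrophage counts are themselves primary outcomes. The cell mix may therefore differ between NAC and placebo.

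If GAPDH moved, all targets in that assay would move together in the same direction. Such agreement among five or six markers could be taken for biological consistency when it came from the denominator. A rise in GAPDH would hide true increases in the same way.

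**Working it through.** The plan gives no figure on this point to reproduce, so the check is a count, some algebra and an illustration.

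**1. Count.** mRNA: Myf5, MyoD, myogenin, MRF4, myostatin = 5. Protein: GPX-3, SOD-2, Trx-1, IGF-1, Notch1, Wnt3 = 6. The total is 11, on two separate GAPDH measurements: the transcript for 5 and the protein for 6.

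**2. Bias within an assay.**
- mRNA: reported fold = true fold × 2^(rise in GAPDH Ct).
- Protein: reported ratio = true ratio ÷ (relative GAPDH level).

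The document gives no size for a GAPDH shift, so the values below are assumptions.

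| Assumed shift | Factor on every target in that assay |
|---|---|
| GAPDH Ct up 0.25 / 0.5 / 1 | 1.19 / 1.41 / 2.00 (all 5 mRNA) |
| GAPDH Ct down 0.25 / 0.5 / 1 | 0.84 / 0.71 / 0.50 (all 5 mRNA) |
| GAPDH protein at 0.9 / 0.8 / 0.7 | 1.11 / 1.25 / 1.43 (all 6 proteins) |
| GAPDH protein at 1.1 / 1.25 | 0.91 / 0.80 (all 6 proteins) |

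A 25% fall gives 1/(1 − 0.25) = 1.33-fold, or −log2(0.75) = 0.415 log2 units. A 10% fall gives 1.11-fold, or 0.152 log2 units.

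**3. Which comparison is affected.** Let GAPDH relative to baseline be g_N in the NAC trial and g_P in the placebo trial at a given time.
- Within-trial time effects are multiplied by 1/g_N or 1/g_P.
- The NAC/placebo ratio is multiplied by g_P/g_N. If g_N = g_P, this is 1 and the bias cancels. If they differ, it does not.

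**4. Illustration of a treatment-dependent shift.** Assume no true effect, 12 men (the planned number per LR or HR group), a paired t-test on log2 values, and an SD of the paired log2 difference between 0.5 and 1.0. The SD is an assumption. The noncentrality is shift × √12 / SD. For a 25% shift and SD 0.5 it is 0.415 × 3.464 / 0.5 = 2.88.

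Probability that a single marker is declared significant:

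| Shift | Level | SD 0.5 | SD 0.75 | SD 1.0 |
|---|---|---|---|---|
| 25% | 0.05 | 0.745 | 0.417 | 0.260 |
| 10% | 0.05 | 0.161 | 0.098 | 0.077 |
| 25% | 0.05/3 | 0.54 | 0.24 | 0.13 |
| 10% | 0.05/3 | 0.07 | 0.04 | 0.03 |

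The plan specifies a two-way repeated-measures ANOVA with Bonferroni-corrected pairwise comparisons. The lower two rows show the effect if the correction covers three comparisons, which is also an assumption. The per-comparison level is then 0.017.

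**The case against.** **Two measurements, not one.** A reader might infer that any GAPDH shift moves all 11 outcomes together. The document does not support that. A transcript shift leaves the six protein outcomes unchanged, and a protein shift leaves the five mRNA outcomes unchanged. All 11 move together only if both references shift in the same direction. This objection stands, and the point is limited to each assay family.

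**Damage is common to both trials.** The same exercise is done in each, so a purely damage-driven shift cancels in the NAC–placebo comparison, which is the study question. This also stands. But time effects are planned comparisons too, and the trial's own premise that NAC alters inflammation means that an equal shift cannot be assumed.

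**No evidence that GAPDH moves.** The Discussion says that "thiol oxidation is a major post-translational oxidative modification affecting the cysteine residues in multiple proteins", but it does not name GAPDH, does not speak of protein abundance and has no bearing on a transcript. It would be wrong to read it as showing that the normalizer is biased. This is an unguarded risk only.

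**Condensed article.** Stability checks are laboratory detail that may sit in the full protocol, and the source cited for the mRNA method is not available here. Absence of a check is therefore weak evidence. What remains is a stated choice: the article fixes one reference per assay.

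**The remedy is imperfect.** Total lane protein also depends on tissue composition, and a significance test on GAPDH has little power. If its own paired log2 SD were 0.5 to 1.0, a 25% shift would be detected with probability only 0.75 to 0.26. Both points are fair. They call for estimation with intervals and for a second reference set beside the first, and they do not favor leaving GAPDH unexamined.

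**Lane load.** The blotting section says "Twenty milligrams of protein will be loaded in gradient precast gels". That is most simply a unit slip. It does not show that GAPDH normalization is biased and should be corrected separately.

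**Conclusion.** The point holds as a cheap improvement to the plan. Each of two primary-outcome families, five mRNA and six protein, depends on one GAPDH reference in a trial that deliberately disturbs redox state and tissue composition. If GAPDH shifts, every target in that family carries the same false factor, 1.11-fold for a 10% fall and 1.33-fold for a 25% fall. A common shift affects time effects only, and a treatment-dependent shift affects NAC versus placebo.

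Under the illustrative assumptions, a treatment-dependent 25% shift would make a null marker significant with probability 0.75 to 0.26 uncorrected, or 0.54 to 0.13 with a three-comparison Bonferroni correction. A 10% shift gives 0.16 to 0.08, or 0.07 to 0.03. The shift sizes, the SDs and the number of comparisons are all assumptions. The document does not establish that any bias will occur.

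**What to change.** 1. **Both assays, before unblinding.** Estimate GAPDH Ct at equal RNA input, and GAPDH band density at equal protein load, by trial, time and trial × time. Report estimates with confidence intervals. Do not treat a non-significant result as proof of stability.
2. **Quantitative RT-PCR.** Add one or two further reference genes on the same cDNA, and normalize to the geometric mean of those found stable. If GAPDH moves, leave it out.
3. **Western blotting.** Normalize to total lane protein by a membrane or gel stain, or prespecify that as a sensitivity analysis beside GAPDH.
4. **Separately**, correct the stated lane load.

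The cost is a few extra primer pairs, a stain, a short stability table and modest bench time. No extra biopsies, visits or staff are needed. The Trial status section says that the trial had not commenced, so the change could be prespecified.
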